#### Assessment

Quantitative and qualitative assessments will be performed before the intervention (T0), immediately after the intervention (T1) and at the six months follow-up (T2). Participants will respond to the same electronic form used in Phase 1 of the study at the three evaluation moments (T0, T1 and T2) and after the intervention they will be able to respond subjectively about their adherence to the sessions, frequency of performing formal practices and report if there were unexpected effects (adverse events) in periods T1 and T2 by completing another electronic form [46]. After six months of follow-up, the control group will be offered the intervention (MBHP or ABCT) considered most effective to improve eating behavior (Fig. 2).

**Fig. 2 fig0002:**
[figure not shown]
Standard Protocol Items: Recommendations for Interventional Trials (SPIRIT) diagram. Abbreviations: MBHP, Mindfulness based Health Promotion; ABCT, Attachment-Based Compassion Therapy; TFEQ-R21, The 21-item Three-Factor Eating Questionnaire; Rep(eat)-Q, Repetitive Eating Questionnaire; BES, Binge Eating Scale; M-A QoLQII, Moorehead-Ardelt Quality of Life Questionnaire II; BSSA, Brazilian Silhouette Scales for Adults; MAAS, Mindful Attention Awareness Scale; SCS, Self Compassion Scale; HADS, Hospital Anxiety and Depression Scale; ECR-R-Brazil, Experiences in Close Relationship Scale – Reduced.

Narrative interviews will be used to produce qualitative data. Unstructured interviews will be conducted in the baseline (T0) with an open trigger question, “Tell me the story of your weight”, on which the participant will be encouraged to speak freely. In (T1) and (T2), the question “What changed in taking care of yourself?” will be added. If needed, the interviewer will direct the dialogue towards “And regarding activities of daily living?”, “And regarding food?”, and lastly “What has changed in your relationship with your body?”. The narrative interviews will be conducted online for about 30 min and statements will be recorded for later transcription and full analysis.

#### Sample size

Sample size estimates indicate that for a 30 % improvement in the primary outcome for groups G1 and G2 and 5 % for group G3 (workshop), with a 95 % bilateral confidence interval and 80 % power, each group will need at least 43 participants. Assuming that 25 % of patients would be lost to follow-up, each group would need 54 patients, with 162 participants in total.

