#### Outcomes

The primary outcome will be a change in the eating behavior (TFEQ-21, Rep (eat)-Q, and BES) at all steps. Secondary outcomes will be improved quality of life (M-A QoLQII), increased satisfaction with body image and reduced distortion (BSSA), better weight management (maintenance or weight reduction), increased frequency of physical activity, and monitoring with the surgery team. The explicative variables will be the level of mindfulness (MAAS), self-compassion (SCS-SF), anxiety (HADS), and attachment style (ECR-R).

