#### Analyses plan

Descriptive statistics will be used to determine the feasibility, acceptability, and effect of Mindfulness-based and compassion-based interventions. The initial baseline characteristics will be revised visually for an approximate balance between groups. For the sociodemographic questionnaire (including the different surgical procedures performed), absolute and relative frequencies will be calculated for categorical variables, whereas means and standard deviations will be estimated for continuous variables.

Statistical procedures will be performed on an intention-to-treat and/or per-protocol basis. For data tabulation and analysis, Excel 2010 programs and SPSS software version 23.0 for Windows (SPSS Inc.; Chicago, IL, USA) will be used. All variables will be subjected to the Kolmogorov-Smirnov test to verify the normal distribution of data. For initial comparisons between the groups, the unpaired *t*-test (two-tailed) or Mann-Whitney U test (two-tailed) will be used for continuous variables whereas Fisher's exact test (two-tailed) and the chi-square test will be used for categorical variables.

After the intervention, a within- and between-group comparative analysis of the scales will be performed with initial and final data using the paired and unpaired *t*-test (two-tailed) for variables with normal distribution (mean, standard deviation, and 95 *%* confidence interval) and the Mann-Whitney U test (two-tailed) for variables with non-normal distribution. Differences between the initial and final means (Δ) of the study variables will be calculated and a comparative analysis of these means will be performed using the *t*-test for independent samples or the Mann-Whitney U test. Statistical procedures will be performed per protocol based on the intention-to-treat analysis. The number needed to treat (NNT) and the number needed to harm (NNH) will be calculated.

To identify the correlation between the study variables and HADS scales, the MAAS, SCS, MAQoLQII, Rep(eat)-Q, TFEQ-R21, BES, ECR-R-Brazil, silhouette scales, and Pearson's and Spearman's correlation coefficient will be used at three time points. At the end of the study, linear regression analyses will be performed with the total sample using complete cases and stratified by weight gain to assess the mediating effect of the statistical relationship between the study scales in the intervention group.

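### The stated 80% power appears to be for a 30% versus 5% difference in responders and does not apply to the planned comparison of mean scale changes

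*Protocol article*

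**What the plan says.** The Sample size section (Phase 2) assumes a 30% "improvement in the primary outcome for groups G1 and G2" and 5% in G3, "with a 95 % bilateral confidence interval and 80 % power", and concludes that "each group will need at least 43 participants". Allowing for 25% loss, it raises this to 54 per group and 162 in total. It does not say whether the percentages are proportions of patients who improve or average percentage reductions in a score.

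The Outcomes section states: "The primary outcome will be a change in the eating behavior (TFEQ-21, Rep (eat)-Q, and BES) at all steps". These are questionnaire scores.

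The Analyses plan compares the scales between groups by unpaired t-test or Mann-Whitney U test. It adds: "Differences between the initial and final means (Δ) of the study variables will be calculated", with these changes compared by the same two kinds of test. Fisher's exact and chi-square tests are named only for the initial comparison of the groups. The section also says: "The number needed to treat (NNT) and the number needed to harm (NNH) will be calculated".

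**The concern.** The sample-size paragraph and the analysis section seem to concern different quantities. One reads like a contrast of two response rates. The other is a contrast of mean changes on a scale. Power computed for the first says nothing directly about the second, which depends on the mean difference relative to its standard deviation.

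The 80% figure is the trial's only quantitative justification for 162 participants. If it does not belong to the test that will be reported, a null result on a scale may be read as coming from a trial with 80% power when its power for that test was never stated. NNT and NNH raise a related difficulty: both need a binary outcome, and none is defined for them.

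**Working it through.** **Inputs.** From the Sample size section: 30% and 5%, two-sided 5%, 80% power, 43 per group, 54 after allowance for 25% loss. From the Analyses plan: independent-samples t-test or Mann-Whitney U on change scores. Normal quantiles: 1.960 and 0.842.

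**1. Reproducing 43 as two proportions.** With p1 = 0.30, p2 = 0.05 and mean proportion 0.175:

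- Uncorrected n = [1.960·√(2·0.175·0.825) + 0.842·√(0.30·0.70 + 0.05·0.95)]² / 0.25² = (1.0532 + 0.4271)² / 0.0625 = 35.06, so 36.
- Continuity-corrected n = (35.06/4)·[1 + √(1 + 4/(35.06·0.25))]² = 8.765·(1 + 1.2068)² = 42.68, so **43**.

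Other two-sided versions give 36 (pooled), 33 (unpooled) and 32 (arcsine). The pooled uncorrected formula at a significance level of 0.025 also gives 43, but the protocol states no such adjustment, and that too is a two-proportion calculation.

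**2. Reading the percentages as mean improvements.** The difference is 25 percentage points. Setting n = 2·[(1.960 + 0.842)·SD/25]² equal to 43 gives SD = 25 / (2.802·√(2/43)) = 25/0.604 = 41.4 points. The protocol states no such SD. The result is sensitive to it (normal approximation, SDs assumed):

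| Assumed SD (points) | n per group for 80% power | Power at 43 per group |
|---|---|---|
| 30 | 23 | 97% |
| 40 | 41 | 83% |
| 50 | 63 | 64% |
| 60 | 91 | 49% |
| 80 | 161 | 30% |

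**3. What the planned t-test can detect.** For a two-sided 5% t-test with 80% power, the standardised difference d is 0.61 at 43 per group. It is 0.63 at 40 per group, the number left if 54 lose 25% (54 × 0.75 = 40.5, rounded down).

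**4. Power of the planned t-test at 40 per group, for assumed d.**

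| d | Power |
|---|---|
| 0.3 | 26% |
| 0.5 | 60% |
| 0.8 | 94% |
| 1.12 | 99.9% |

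The last row is the d implied by 30% versus 5% responders. If change is normal with equal variance in both arms and response means passing a common cut-off, the cut-off lies 1.645 SD above the control mean (5% beyond it) and 0.524 SD above the program mean (30% beyond it). Hence d = 1.645 − 0.524 = 1.12.

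**The case against.** The strongest reply is that the binary basis is inferred. The protocol never mentions a proportion or a responder, a match on one formula variant is not proof, and mean improvements with an SD near 41 points would also give 43. That stands: the binary reading is very likely but not confirmed. It does not rescue the 80%, because under the other reading the stated inputs do not determine a sample size at all.

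A second reply is that a condensed article may leave an SD or a response definition to a fuller document. That also stands, so the missing SD is not itself the point. The point is that the figures in one section do not fit the test named in another.

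A reader might infer that the trial is underpowered. The protocol does not support this. It fixes no standardised effect, and if 30% versus 5% responders were true under the normal model above, the t-test would have far more than 80% power. Whether so large an effect is plausible is a separate question.

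A reader might also infer that NNT must rest on a cut-off picked after seeing the data. That is possible but not necessary. The Measurements section already gives Binge Eating Scale bands (up to 17, 18 to 26, 27 and above), and that scale is one of the primary instruments. The protocol simply does not link NNT or NNH to them.

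Finally, the trial calls itself a feasibility study of preliminary effectiveness. This lowers the stakes but does not remove the mismatch, since the document makes the 80% claim itself.

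**Conclusion.** The concern holds as a mismatch between the power statement and the planned analysis. The 43 per group matches a two-proportion calculation (42.68), while the primary outcome is change in scale scores compared by t-test or Mann-Whitney with no responder endpoint. The stated 80% power does not carry over to that comparison.

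Actual power could be lower or higher: roughly 26% to 99.9% at 40 per arm for d between 0.3 and 1.12. All these d values are assumptions, and the value 1.12 further assumes normal, equal-variance change. The power figures are for the t-test. The finding is that the power of the planned analysis is unstated, not that it is inadequate. Given the feasibility setting, this should be fixed but is not critical.

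**What to change.** Restate the sample-size paragraph for the analysis planned, for example: *with 40–43 analysed per arm, each program-versus-workshop comparison of mean change on a scale has 80% power at two-sided 5% for a standardised difference of 0.63–0.61.* This describes what the existing size can detect on any one scale. It does not choose among the three instruments or justify the effect as a target, and the investigators should say whether a difference of that size is realistic.

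Alternatively, if a responder endpoint was intended, define it in advance, name its scale and threshold, and state the between-group test, so that the 30% and 5% figures have an endpoint to refer to.

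In either case, tie NNT and NNH to a pre-specified cut-off, for example the Binge Eating Scale bands already in the Measurements section, or delete them.

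The first option is a change of wording. The second also needs a decision on the endpoint. Neither calls for more participants. The price is that the detectable effect becomes explicit and open to challenge.

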### Phase 2: clinical trial

#### Trial design

This is a randomized controlled clinical trial of mixed methods with random allocation in three groups: G1 (MBHP + workshops); G2 (ABCT + workshops); and G3 (workshops), with patients who underwent gastroplasty and regained weight from the clinic already mentioned.

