#### Recruitment

The participants who answer the questionnaire of Phase 1 and match the criteria specific to Phase 2 will be recruited, as well as other patients that will continue to be recruited at the clinical headquarters by doctors and other health professionals from the multidisciplinary team and on the social networks of the referred clinic. It is expected that it will take 3 recruitment rounds of each intervention group to reach 54 participants per group. For better engagement during the intervention, online interaction groups will be formed for all groups (G1, G2 and G3) and participants who miss a session or a workshop will be contacted individually.

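### The allowance for 25% loss multiplies 43 by 1.25 instead of dividing by 0.75, so 54 per group leaves 40 to 41 participants, short of the plan's own minimum of 43

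*Protocol article*

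**What the plan says.** The Sample size section for Phase 2 (Protocol article) plans for a 30% improvement in the primary outcome in each of the two programme groups and 5% in the workshop group, "with a 95 % bilateral confidence interval and 80 % power". On that basis "each group will need at least 43 participants".

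The allowance for attrition follows: "Assuming that 25 % of patients would be lost to follow-up", the section concludes that "each group would need 54 patients, with 162 participants in total".

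The Trial design section confirms "random allocation in three groups". The Recruitment section carries the result forward as the operational target, expecting "3 recruitment rounds of each intervention group to reach 54 participants per group". The article gives no other loss rate and no other inflation rule.

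**The concern.** The percentage is stated as a share of the patients who enter, so the number still under observation is the enrolled number times 0.75. To end with 43, the plan must divide 43 by 0.75. Adding 25% to 43 is a different operation and always gives too small a number, because a quarter of the larger enrolled group is more than a quarter of 43.

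If the plan's own attrition assumption comes true, every group therefore finishes below the minimum that the same section sets. The figure is also in use: the recruitment rounds are planned around it.

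**Working it through.** **Inputs** (Sample size section unless noted)
- Minimum per group: 43
- Loss to follow-up: 25% of patients
- Enrolled: 54 per group, 162 in total
- Groups: 3 (Trial design)
- Two-sided 5% level, 80% power, 30% versus 5%

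**Step 1. Reproduce the 43.** The section does not name its formula. As an assumption, read 30% and 5% as the proportions of participants who improve. The mean proportion is 0.175 and the difference is 0.25.

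- Without continuity correction: n = [1.96 × √(2 × 0.175 × 0.825) + 0.842 × √(0.30 × 0.70 + 0.05 × 0.95)]² / 0.25² = 35.1, rounded up to 36.
- With continuity correction: n = (35.1 / 4) × [1 + √(1 + 4 / (35.1 × 0.25))]² = 42.7, rounded up to **43**.

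The continuity-corrected formula matches the stated minimum. The match is not unique: a level of 0.025 without the correction also gives 43. Nothing in steps 2 to 4 depends on how 43 was obtained.

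**Step 2. Reproduce the 54.**
- 43 × 1.25 = 53.75, rounded up to **54**; 3 × 54 = 162. Both stated figures are matched.
- 43 / (1 − 0.25) = 57.33, rounded up to **58**; 3 × 58 = 174, which is 12 more than stated.

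Rounding cannot account for a gap of four per group.

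**Step 3. Check each number against the minimum of 43.**
- 54 × 0.75 = 40.5, so 40 or 41 remain: 2 to 3 short.
- 57 × 0.75 = 42.75: just short.
- 58 × 0.75 = 43.5: sufficient.

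**Step 4. Loss that 54 can absorb.** (54 − 43) / 54 = 11 / 54 = 20.4%.

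**Step 5. What the shortfall means for power.** The comparison is 30% versus 5%, two-sided 5%, again reading these as proportions improved.

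| Calculation | 40 per group | 41 per group | 43 per group |
|---|---|---|---|
| Continuity-corrected formula | 76.7% | 78.0% | 80.4% |
| Fisher's exact test (full enumeration) | 82.1% | 83.4% | 84.4% |
| Uncorrected chi-square | 85.1% | 86.0% | 87.6% |

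With a level of 0.025 and no correction, power at 40 per group is 77.1%. The loss of power relative to 43 is about 2 to 4 percentage points in every row of the table. Whether it crosses 80% depends on the row.

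**The case against.** The strongest reply is that little follows in practice. The shortfall is 2 to 3 people per group. The 25% is a planning guess, and at a loss of 20.4% or less 54 is enough. The Recruitment section plans measures against loss: online interaction groups in all arms and individual contact after a missed session. The specifications table calls Phase 2 a feasibility study, and its aim is preliminary evidence. The slip biases no estimate and does not affect type I error. All of this stands, and it limits the weight of the point. It does not make the printed figures agree.

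A reader might go further and infer that the trial is underpowered, or that 54 per group, 25% loss and 80% power cannot coexist. The document does not support that. The Sample size section names no test. Fisher's exact test and the chi-square test are the only tests for proportions that the Analyses plan names (there for initial comparisons), and under both, power at 40 per group stays above 80%. Moreover, the Outcomes section defines the primary outcome as change on three eating-behaviour questionnaires, and the Analyses plan compares scales by t-test or Mann-Whitney test. No power computed from two proportions is therefore the power of the planned comparison.

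It might also be said that intention-to-treat analysis makes the number of completers irrelevant. But the Sample size section itself enlarges the groups to offset loss to follow-up, so it treats lost patients as reducing the usable sample. Nor is this a detail left to a fuller document: the minimum, the loss rate and the enrolled number are all printed, and they conflict.

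**Conclusion.** The point holds as an arithmetic error in a stated figure. A minimum of 43, a loss of 25% and an enrolment of 54 cannot all be true. At the stated loss rate 54 per group is 4 too few (58 needed), and the total is 12 too few (174 instead of 162). This rests only on the plan's own numbers and on reading the 25% as a share of patients enrolled, as the sentence words it.

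The effect on power is small and conditional. It falls to about 77% at 40 per group under the continuity-corrected formula that reproduces 43, but stays at about 82% with Fisher's exact test and 85% with the uncorrected chi-square. All three rest on the assumption that 30% and 5% are proportions improved. A failure to reach 80% power is therefore not shown, and 77% should not be presented as the trial's power. This is a small correction.

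**What to change.** Correct the sentence in the Sample size section. The least costly version keeps 54 per group (162 in total) and states that this yields 43 completers only if loss is at most about 20%, and that at 25% loss about 40 per group remain. The cost is one sentence and a slightly less favourable statement of tolerated attrition; recruitment does not change.

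If the sponsor prefers to keep both the 25% loss and the 43 completers, state 58 per group (174 in total) and replace the 54 in the Recruitment section. This costs 12 more participants and a check that the three planned recruitment rounds can supply them.

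Any power quoted for 40 per group should name the method and the outcome definition on which it was calculated.

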#### Recruitment

The participants who answer the questionnaire of Phase 1 and match the criteria specific to Phase 2 will be recruited, as well as other patients that will continue to be recruited at the clinical headquarters by doctors and other health professionals from the multidisciplinary team and on the social networks of the referred clinic. It is expected that it will take 3 recruitment rounds of each intervention group to reach 54 participants per group. For better engagement during the intervention, online interaction groups will be formed for all groups (G1, G2 and G3) and participants who miss a session or a workshop will be contacted individually.

#### Data management

The information from this research will be stored in secure folders with limited access. Information from this survey will be stored in secure folders with limited access. The files will be password protected at Research Electronic Data Capture, a platform for collecting, managing and disseminating research data (REDCap), signed by the Federal University of São Paulo (UNIFESP). The list with participant numbers and personal information will be stored in a password-protected file. To avoid some risk of negligence, there will be an assignment of a data monitoring committee. Only the main investigators, or people designated by them, will have access to all the final data. Data will be stored for five years after the inclusion ends. Study participants, funders, and professionals involved will receive a summary of the study's results.

#### Analyses plan

Descriptive statistics will be used to determine the feasibility, acceptability, and effect of Mindfulness-based and compassion-based interventions. The initial baseline characteristics will be revised visually for an approximate balance between groups. For the sociodemographic questionnaire (including the different surgical procedures performed), absolute and relative frequencies will be calculated for categorical variables, whereas means and standard deviations will be estimated for continuous variables.

Statistical procedures will be performed on an intention-to-treat and/or per-protocol basis. For data tabulation and analysis, Excel 2010 programs and SPSS software version 23.0 for Windows (SPSS Inc.; Chicago, IL, USA) will be used. All variables will be subjected to the Kolmogorov-Smirnov test to verify the normal distribution of data. For initial comparisons between the groups, the unpaired *t*-test (two-tailed) or Mann-Whitney U test (two-tailed) will be used for continuous variables whereas Fisher's exact test (two-tailed) and the chi-square test will be used for categorical variables.

After the intervention, a within- and between-group comparative analysis of the scales will be performed with initial and final data using the paired and unpaired *t*-test (two-tailed) for variables with normal distribution (mean, standard deviation, and 95 *%* confidence interval) and the Mann-Whitney U test (two-tailed) for variables with non-normal distribution. Differences between the initial and final means (Δ) of the study variables will be calculated and a comparative analysis of these means will be performed using the *t*-test for independent samples or the Mann-Whitney U test. Statistical procedures will be performed per protocol based on the intention-to-treat analysis. The number needed to treat (NNT) and the number needed to harm (NNH) will be calculated.

To identify the correlation between the study variables and HADS scales, the MAAS, SCS, MAQoLQII, Rep(eat)-Q, TFEQ-R21, BES, ECR-R-Brazil, silhouette scales, and Pearson's and Spearman's correlation coefficient will be used at three time points. At the end of the study, linear regression analyses will be performed with the total sample using complete cases and stratified by weight gain to assess the mediating effect of the statistical relationship between the study scales in the intervention group.

The laminates are established from less postoperative weight in the first year, as follows: 1 to 10 % weight regained from 11 to 20 %, etc. The level of significance will be 5 % (*p* < 0.05) in all tests.

The qualitative data will be analyzed using the thematic content analysis technique [47]. The NVivo software (version 12) will be used for this organization and treatment. Data will be treated by lexical coding, thematic analysis, and association between linguistic, paralinguistic, and sociodemographic variables.

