## Conclusion

This study seeks to gather preliminary evidence on the effectiveness of mindfulness and compassion training for the adjunctive treatment of progressive weight gain in post-bariatric patients.

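### A normality pre-test picks the test for each primary eating score, and a 95% confidence interval is named only for scores judged normal

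*Protocol article*

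**What the plan says.** All of the rule stands in the Phase 2 Analyses plan of the protocol article.

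- Pre-test: "All variables will be subjected to the Kolmogorov-Smirnov test to verify the normal distribution of data".
- If normal: paired and unpaired t-tests "for variables with normal distribution (mean, standard deviation, and 95" percent confidence interval).
- If not normal: "the Mann-Whitney U test (two-tailed) for variables with non-normal distribution". No estimate or interval is named with it.
- For all variables: "Differences between the initial and final means (Δ) of the study variables will be calculated and a comparative analysis of these means will be performed", by t-test or Mann-Whitney U. The calculation of Δ carries no normality condition.
- Also for the trial: "The number needed to treat (NNT) and the number needed to harm (NNH) will be calculated".
- The significance level is 5% in all tests.

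The Outcomes section shows what the rule acts on: "The primary outcome will be a change in the eating behavior (TFEQ-21, Rep (eat)-Q, and BES) at all steps". According to the Measurements section, these instruments yield three TFEQ-R21 factors, a Rep(eat)-Q overall mean with two domain scores, and a BES total. That is up to 3 + 3 + 1 = 7 scores. They are assessed at T1 and T2 in three arms.

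**The concern.** The t-test and the Mann-Whitney U test answer different questions. One concerns a difference in means, the other a tendency for values in one arm to exceed those in the other. Here a significance test on the trial's own data decides which question is asked of each score. The primary scores, which are meant to be read together, can therefore end with different tests and different summaries, and nobody can say which until the data are in.

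The interval is the larger loss. The Conclusion says: "This study seeks to gather preliminary evidence on the effectiveness of mindfulness and compassion training". Evidence of that kind is mainly useful as an estimate with its uncertainty, which a later trial can plan from. The plan names the interval only for scores that pass the pre-test. It also leaves open whether normality is judged per arm or pooled, and on raw or change scores. Those choices can flip the method.

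**Working it through.** **Sample size to use.** The article plans 43 per group (30% against 5% improved, two-sided 5%, 80% power). Reproducing it:

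- Mean proportion: (0.30 + 0.05)/2 = 0.175.
- Uncorrected: n = [1.96·√(2·0.175·0.825) + 0.8416·√(0.30·0.70 + 0.05·0.95)]² / 0.25² = 35.06, so 36.
- With continuity correction: (35.06/4)·[1 + √(1 + 4/(35.06·0.25))]² = 42.7, so 43. This matches.

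The checks use n = 43 (planned minimum per arm), 54 (recruited per arm) and 162 (all arms pooled).

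**How often the pre-test rejects normality.** The article gives no distribution for any scale, so skewness is an assumption (normal and gamma shapes, range 0 to 2). The figures come from 1,000 simulated raw-score samples per cell, tested at 5%. The first figure has the Lilliefors correction for estimated mean and SD; the figure in brackets is uncorrected.

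| Assumed skewness | n = 43 | n = 54 | n = 162 |
|---|---|---|---|
| 0 (normal) | 6% (0%) | 5% (0%) | 4% (0%) |
| 0.5 | 12% (0%) | 15% (0%) | 29% (1%) |
| 1.0 | 32% (1%) | 40% (2%) | 86% (28%) |
| 1.4 | 62% (5%) | 74% (10%) | 100% (72%) |
| 2.0 | 92% (26%) | 97% (45%) | 100% (100%) |

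At skewness 1.0 the same score meets rejection rates from about 1% to 86%, depending only on the test variant and on pooling.

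**Raw or change scores.** With an assumed correlation of 0.6 between visits, the corrected test on change scores rejects in about 11% (skewness 1.0) and 23% to 27% (skewness 1.4) at arm-level n. Pooled at n = 162, the rates are about 19% to 21% and 58% to 60%. These are well below the raw-score rates.

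**What the switch does to inference.** Two arms of 43 were simulated 4,000 times per scenario, with the corrected pre-test applied to each arm.

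- Type I error of the two-stage procedure: 4.9% to 5.2% for skewness 0 to 2.
- The t-test and Mann-Whitney U test disagree on significance in 1.7% to 4.0% of null trials (skewness 0 to 2), and in 5.7% to 10.6% with a shift of 0.6 SD (skewness 0 to 1.4).

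**Is the pre-test needed to protect the interval?** In the same simulation the t-based 95% confidence interval for the mean difference, used whatever the pre-test says, covered the true value in about 94.9% to 95.6% of trials for skewness 0 to 2. It is not needed.

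**The case against.** The case on the other side has four parts.

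1. **Effect estimates are not absent.** A reader might infer that a skewed score yields a p-value alone. The Analyses plan contradicts this: it plans Δ of means without a normality condition, and NNT and NNH. What remains is narrower. The comparison of Δ is again by t-test or Mann-Whitney U, with no interval attached, and no responder definition is given for the NNT.

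2. **The choice is not a coin toss in general.** A reader might also infer that the method is set close to chance, or that T1 and T2 would often receive different tests. Both need assumed skewness of about 1.0 to 1.4, raw scores, arm-level testing and the Lilliefors correction. Near-normal or strongly skewed scores mostly fall one way under the corrected test. The article does not say that the method is chosen afresh at each visit, so no discordance rate between visits can be claimed. This objection stands in full.

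3. **Error rates are sound, and Mann-Whitney U is a valid test for skewed questionnaire scores.** This is true. The point is not that the trial would produce false positives.

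4. **The article is condensed, and an interval for the rank branch may be specified elsewhere.** That is possible. But the article does state the selection rule and does place the interval in the normal branch only. The point concerns that stated rule.

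**Conclusion.** The point holds as one of estimation, comparability and pre-specification. A pre-test on trial data chooses the method for each primary eating score, and a score judged non-normal has no stated between-group estimate with a confidence interval. The documents do not support calling the choice random, the effect estimates missing, or the type I error inflated.

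The size cannot be fixed from the article, because skewness, test variant, pooling and the type of score are all unstated. At assumed skewness 1.0 on raw scores, a switch to the rank test would occur in about 32% (n = 43) to 86% (n = 162) of samples with the corrected test, and in about 1% to 28% with the uncorrected test. Change scores would switch less often. Where a switch occurs, the practical loss is the interval and a common scale of reporting. The significance verdict itself would usually be the same. This is a cheap improvement worth making, not a threat to the trial's validity.

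**What to change.** Delete the normality pre-test as a selector of method. For every primary scale at T1 and T2, report the between-arm mean difference with a 95% confidence interval whatever the distribution, preferably from a baseline-adjusted linear model, with bootstrap or robust standard errors if residuals are skewed. Keep the Mann-Whitney U test as a stated sensitivity analysis for all primary scales.

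The cost is analysis wording only; no sample size changes. The downside is some power when scores are strongly skewed. In the simulation with a 0.6 SD shift and 43 per arm, the rank test had 89.0% power against 79.8% for the t-test at skewness 1.4, but 76.1% against 78.6% for normal data. The sensitivity analysis would still show such a result.
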